# Multicenter phase III randomized trial comparing laparoscopy and laparotomy for colon cancer surgery in patients older than 75 years: the CELL study, a Fédération de Recherche en Chirurgie (FRENCH) trial

**DOI:** 10.1186/s12885-019-6376-8

**Published:** 2019-12-04

**Keywords:** Elderly patient, Colon cancer, Surgery, Laparoscopy, Laparotomy, Morbidity, Phase III trial

## Abstract

**Background:**

Several multicenter randomized controlled trials comparing laparoscopy and conventional open surgery for colon cancer have demonstrated that laparoscopic approach achieved the same oncological results while improving significantly early postoperative outcomes. These trials included few elderly patients, with a median age not exceeding 71 years. However, colon cancer is a disease of the elderly. More than 65% of patients operated on for colon cancer belong to this age group, and this proportion may become more pronounced in the coming years. In current practice, laparoscopy is underused in this population.

**Methods:**

The CELL (Colectomy for cancer in the Elderly by Laparoscopy or Laparotomy) trial is a multicenter, open-label randomized, 2-arm phase III superiority trial. Patients aged 75 years or older with uncomplicated colonic adenocarcinoma or endoscopically unresectable colonic polyp will be randomized to either colectomy by laparoscopy or laparotomy. The primary endpoint of the study is overall postoperative morbidity, defined as any complication classification occurring up to 30 days after surgery. The secondary endpoints are: 30-day and 90-day postoperative mortality, 30-day readmission rate, quality of surgical resection, health-related quality of life and evolution of geriatric assessment. A 35 to 20% overall postoperative morbidity rate reduction is expected for patients operated on by laparoscopy compared with those who underwent surgery by laparotomy. With a two-sided α risk of 5% and a power of 80% (β = 0.20), 276 patients will be required in total.

**Discussion:**

To date, no dedicated randomized controlled trial has been conducted to evaluate morbidity after colon cancer surgery by laparoscopy or laparotomy in the elderly and the benefits of laparoscopy is still debated in this context. Thus, a prospective multicenter randomized trial evaluating postoperative outcomes specifically in elderly patients operated on for colon cancer by laparoscopy or laparotomy with curative intent is warranted. If significant, such a study might change the current surgical practices and allow a significant improvement in the surgical management of this population, which will be the vast majority of patients treated for colon cancer in the coming years.

**Trial registration:**

ClinicalTrials.gov NCT03033719 (January 27, 2017).

## Background

Colorectal cancer (CRC) is the third site of cancer worldwide with over 1.2 million new diagnosed cases annually [1]. Colon cancer is a disease of the elderly. Patients older than 85 years are three times more likely to develop colon tumors than those aged between 60 and 69 years [2]. The proportion of elderly patients managed for colon cancer can only increase in the future, due to the increase in life expectancy and the aging of the general population [3, 4].

Several randomized trials have demonstrated that colon cancer surgery should be performed by laparoscopy [5, 6]. Compared to open surgery, laparoscopic approach significantly improves postoperative recovery and short-term outcomes [7–15], with no adverse effect on long-term oncological outcomes [16–21]. However, patients recruited in these phase III trials were significantly younger that patients operated on in daily practice, with a median age not exceeding 71 years [7–15]. We can hypothesize that benefit of mini-invasive surgery is even more pronounced in frailer, older colon cancer patients because of improved postoperative comfort, lesser postoperative analgesics consumption and earlier recovery compared to open usrgery. However, laparoscopy has been consistently associated with longer operative duration and, whether this negatively affects outcome by increasing geriatric complications including postoperative delirium in the elderly is unknown. When we look at surgical practices, we see that the age of patients has an influence on the approach used. In a recent French survey of more than 84,000 patients who underwent colorectal resection for cancer between 2006 and 2008 and based on data from the national prospective database French Medical Information System (PMSI, *Programme de Médicalisation des Systèmes d’Information*), Panis and colleagues [22] reported that patients older than 70 years were significantly less operated by laparoscopy compared with younger patients (21.7% vs. 32.9%, *p* < 1.10–6). Therefore, as elderly patients have been excluded from the major studies that led to the development of guidelines for the surgical management of colon cancer, whether these recommendations can be extrapolated to the elderly population or not is unknown.

## Methods/design

### Protocol overview

The CELL (Colectomy for cancer in the Elderly by Laparoscopy or Laparotomy) trial is a multicenter, open-label randomized, 2-arm phase III superiority trial comparing laparoscopic or open colectomy in elderly patients operated on for colon cancer. For all patients likely to be included in this trial, a comprehensive geriatric assessment (CGA) must be performed within 30 days before the randomization by a geriatrician of the investigator center. This multidimensional evaluation is a major consideration in assessment of operative risk, treatment decision-making, and adapting perioperative care if surgery is undertaken. It aims to determine the medical, psychological and functional capabilities of elderly persons and to distinguish the weakest patients. This diagnostic process will include several reproducible and internationally validated tools, with at least the following scores: the Mini Mental State (MMS) test, the Katz Activities of Daily Living (ADL) scale, the Lawton Instrumental Activites of Daily Living (IADL) scale, the Geriatric Depression Scale (GDS), and the Timed Get-up-and-go (TGUG) test. The general treatment plan is given in Fig. 1.

**Fig. 1 Fig1:**
[figure not shown]
Temporal sequence of trial conduct in patients included in this trial

### Inclusion criteria

For inclusion in the study, all of the following inclusion criteria must be fulfilled: (i) age ≥ 75 years; (ii) histologically proven colonic adenocarcinoma (> 15 cm from the anal margin) or endoscopically unresectable colonic polyp; (iii) uncomplicated primary tumor (preoperative suspicion of invasion of adjacent structures by the colon cancer (cT4) on CT scan, tumor perforation, obstruction, abscess, bleeding); (iv) no history of colorectal cancer in the last 5 years; (v) no peritoneal carcinomatosis on abdominal CT scan; (vi) patient able to fill in an auto-questionnaire alone or with some help; (vii) patient who has signed an informed consent form prior to randomization and who commits himself or herself to respect the protocol instructions; (viii) positive CGA and MMS (Mini Mental Score) ≥ 15.

### Exclusion criteria

Patients are not eligible for this study if any of the following exclusion criteria apply: (i) rectal cancer (≤ 15 cm from the anal verge); (ii) locally advanced (cT4 tumor) or complicated primary tumor requiring extended local resection or emergency surgery; (iii) synchronous colorectal cancer; (iv) scheduled need for synchronous intra-abdominal surgery, including surgery for liver metastases; (v) absolute contraindications to general anesthesia or prolonged pneumoperitoneum; (vi) patient not able to tolerate colon surgery according to the CGA; (vii) estimated life expectancy less than 6 months; (viii) patient under guardianship; (ix) other known active cancer (except nonmelanomatous skin cancer); (x) patient not affiliated to the social security system.

### Endpoints

The main endpoint of this phase III study is overall postoperative morbidity, defined as any surgical or medical complications occurring up to 30 days after the surgery. If a patient is discharged from the hospital before this delay, an appointment for an outpatient visit will be given at the 30th postoperative day to finish completing the postoperative morbidity form. Postoperative morbidity will be collected by an independent observer, using a standardized collection form during hospitalization and eventual subsequent out-patient visits. The following specific complications will be documented:
Geriatric complications: postoperative delirium, need for physical restraint, fecal impaction, bedsore, fall, swallowing disorder.Postoperative transfusion.Abdominal infectious complications: anastomotic leakage, intra-abdominal collection at a distance from the anastomosis, wall abscess or cellulitis.Non-infectious abdominal complications: paralytic ileus, hematoma, hemoperitoneum, gastrointestinal bleeding, evisceration.Medical complications: cardiovascular complications including cardiac arrest, acute coronary syndrome without myocardial infarction, myocardial infarction, acute heart failure, heart rhythm disorder, transient ischaemic attack or stroke or other; pulmonary complications including pneumonia, pulmonary embolism, acute respiratory failure, pleural effusion or other; deep vein thrombosis; urinary and nephrological complications including acute urinary retention, lower urinary tract infection, pyelonephritis, acute renal failure or other; catheter complications including lymphangitis, thrombosis, infection or other.

The occurrence of postoperative delirium is a specific complication reported in elderly patients after surgery [23]. This complication will be specifically assessed using the Confusion Assessment Method, an instrument validated for the diagnosis of delirium [24]. Anastomotic leakage will be defined either with the clinical findings of peritonitis or radiologically by computed tomography scan with water-soluble rectal contrast demonstrating endoluminal extravasation or isolated intra-abdominal abscess close to the anastomosis. It will be recorded even if it did not involve surgical management. Post-operative complications will be graded from 0 to V based on the classification system validated by Clavien and Dindo [25].

Secondary endpoints are the following: (i) 30-day and 90-day postoperative mortality; (ii) readmission rate. A readmission will be defined in both arms as any rehospitalization within 30 days after discharge from the hospital; (iii) quality of surgical resection. Surgical resection, performed either by laparoscopy or laparotomy, must achieve oncological quality criteria recommended by the French Federation of Digestive Oncology (FFCD, *Fédération Française de Cancérologie Digestive*) and by the French National Authority for Health (HAS, *Haute Autorité de Santé*). Quality and radicality of the surgical excision will be evaluated on histological criteria (number of lymph nodes harvested, R0 resection and mesocolic resection quality in 3 grades); (iv) health-related quality of life. Quality of life will be assessed using the French version the European Organization for Research and Treatment of Cancer Quality of Life Questionnaire Core 30 (EORTC QLQ-C30) version 3.0, with the specific CRC module (QLQ-CR29) [26, 27]. Quality of life will be assessed at the inclusion before surgery and 3 months postoperatively in both treatment arms. The QLQ-C30 consists of 30 items with both multi-items scales and single item measures. The internal validation of QLQ-C30 allowed to identify 15 scales and to generate 15 scores: 5 scores of functional scale, a global health status scale and 9 symptoms scale. All EORTC QLQ-C30 raw scores will be linearly transformed to a value ranging from 0 to 100 according to the EORTC scoring manual. For the 5 functional scales (physical, role, cognitive, emotional and social) and global quality of life scale, a higher score represents a higher level of functioning or quality of life. For the 9 symptom scales and items (fatigue, nausea and vomiting, pain, dyspnea, sleep disturbance, appetite loss, constipation, diarrhea and financial difficulties), a higher score corresponds to a higher degree of symptoms; (v) evolution of geriatric scores (MMS, ADL scale, IADL scale, GDS and TGUG test) at 3 months postoperatively in both arms.

All data of interest will be entered electronically on the Cleanweb site and stored in the patient’s file. An auditing trial will be performed by the Clinical Research Unit of Pitié-Salpêtrière hospital at least twice in each participating center.

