### Randomization

After completion of all the screening evaluations and the CGA, a second visit will be performed. All eligible patients will be randomly assigned to one of the treatment arms after ensuring that all the inclusion criteria are satisfied, none of the exclusion criteria apply, and the patient gave his nonopposition to participate in the study. The randomization will be performed electronically on the Cleanweb site (https://cleanweb.aphp.fr/Ctms-02/portal/login). To obtain homogeneous populations among treatment arms, patients will be randomized by minimization (in a 1:1 ratio) owing to the following stratification factors: (i) investigator center; (ii) colon tumour location (right or left side, with respect to the splenic flexure); (iii) stage IV colon cancer (excluding peritoneal disease); (iv) age (75–85 years vs. >85 years).

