### Intraoperative and postoperative management

Neither patients nor health-care providers will be blinded to patient groupings.

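### The readmission endpoint counts booked admissions together with returns for complications, which can dilute a difference between the arms (minor)

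*Protocol article*

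**What the plan says.** The Protocol article, Endpoints, lists readmission as a secondary endpoint and defines it: "A readmission will be defined in both arms as any rehospitalization within 30 days after discharge from the hospital". The abstract calls it the "30-day readmission rate" without naming the start of the window, which is compatible with this definition.

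Three other places bear on which admissions can fall into the window:

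- Randomization: one of the minimization factors is "stage IV colon cancer (excluding peritoneal disease"), so patients with metastatic disease are eligible.
- Exclusion criteria: the relevant exclusion is "scheduled need for synchronous intra-abdominal surgery, including surgery for liver metastases". It concerns surgery planned together with the colectomy, not a later admission.
- Intraoperative and postoperative management: "Neither patients nor health-care providers will be blinded to patient groupings".

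The article does not separate planned from unplanned readmissions. It gives no readmission rate, length of stay, chemotherapy schedule or share of stage IV patients.

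**The concern.** The rule is stated in full, so this is not a detail that the article left to a longer document. A site that applies it must count every hospital stay that begins in the window. In a cancer population, some of those stays may be booked in advance and say nothing about how the patient recovered from the colectomy.

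Readmission stands beside mortality and morbidity as a short-term outcome of the surgical approach, and a reader will take a higher rate as worse. If scheduled cancer care is mixed in at the same rate in both arms, the observed difference is smaller and noisier than the difference in complication-related returns. The trial could then report similar readmission although the returns that matter differ.

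**Working it through.** **The plan's own figure.** The only sample size calculation is for the primary endpoint (Statistical analysis and sample size: 35% versus 20%, two-sided 5%, power 80%). With pooled variance under the null and mean rate 0.275:

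n = [1.96·√(2·0.275·0.725) + 0.8416·√(0.35·0.65 + 0.20·0.80)]² / 0.15² = (1.2377 + 0.5239)² / 0.0225 ≈ 137.9, so 138 per arm and 276 in total.

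The stated figure reproduces exactly. The document makes no power claim for readmission, so there is nothing to reproduce there.

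**Inputs for the illustration.** The 138 per arm and the two-sided 5% level come from the document. The readmission rates and planned-admission rates are assumptions.

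**Effect of planned admissions.** Let p be the unplanned readmission rate and c the probability of a planned admission in the window, independent of p and equal in both arms. The rate under the stated definition is

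p′ = 1 − (1 − p)(1 − c),

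so the difference between arms is multiplied by (1 − c). Power is approximated by

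Φ{ [|d| − 1.96·√(2p̄(1 − p̄)/n)] / √[(p₁(1 − p₁) + p₂(1 − p₂))/n] }.

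For 6% versus 14% with c = 0: √(2·0.10·0.90/138) = 0.0361 and the denominator is 0.0358, so (0.080 − 1.96·0.0361)/0.0358 ≈ 0.26 and Φ ≈ 0.60.

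| Planned, both arms | Rates counted | Difference | Power |
|---|---|---|---|
| 0% | 6.0% vs 14.0% | 8.0 points | 60% |
| 5% | 10.7% vs 18.3% | 7.6 points | 43% |
| 10% | 15.4% vs 22.6% | 7.2 points | 33% |
| 15% | 20.1% vs 26.9% | 6.8 points | 26% |

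With unpooled variance the last row is 27%. The difference itself shrinks little; most of the lost power comes from the higher variance at higher rates.

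**Sensitivity to the assumed rates.** The same calculation with 0%, 5%, 10% and 20% planned admissions gives:

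- Unplanned 5% versus 12%: power 55%, 37%, 28% and 18%.
- Unplanned 8% versus 12%: power 20%, 14%, 12% and 9%. The difference goes from 4.0 to 3.8, 3.6 and 3.2 points.

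The direction is the same throughout. With a small true difference, the comparison is weak even before any planned admission is added.

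**The case against.** **Contamination is unproven and probably balanced.** The document never mentions planned oncological admissions, and that they fall within 30 days of discharge is an assumption. Stage IV is a minimization factor, so the patients most likely to have them should be evenly spread. This stands as to size and makes bias unlikely. It does not remove dilution, which is what equal rates in both arms produce.

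**All-cause counting needs no judgement.** Care is open-label, so a planned/unplanned label would be applied by staff who know the arm. This is a real cost of the fix and the reason to keep the all-cause rate.

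**Stronger readings a reader might infer.**

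- *The window should not start at discharge, because laparoscopy may bring discharge forward.* The Background does hypothesise "improved postoperative comfort, lesser postoperative analgesics consumption and earlier recovery compared to open" surgery, but gives no length of stay. A discharge start gives every discharged patient the same 30 days at risk. A window closing on a fixed postoperative day would not: with assumed stays of 6 and 9 days, closing at day 30 leaves 24 versus 21 days at risk, and closing at day 90 leaves 84 versus 81. This is a trade-off, not an error, even though the primary endpoint is counted from surgery ("defined as any surgical or medical complications occurring up to 30 days after the surgery").
- *The day-30 visit cuts observation short, and by different amounts in the two arms.* That visit has another stated task: "an appointment for an outpatient visit will be given at the 30th postoperative day to finish completing the postoperative morbidity form". The Endpoints section also sets 3-month assessments and 90-day mortality. On the same assumed stays the readmission windows close on days 36 and 39, well before 3 months. Nothing says that readmissions stop being recorded at day 30.
- *The definition creates an artificial difference.* One can be constructed: if 10% to 30% of patients have a planned admission spread evenly over postoperative days 28 to 56, a 3-day difference in discharge adds 3/28 of that share, or 1.1 to 3.2 points, to the later-discharged arm. Every input is assumed, so the document does not show such a difference.
- *Patients who die before discharge count as not readmitted.* The article does not say how they are counted, and that can be left to the full protocol or analysis plan.

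**Conclusion.** The point holds in a limited form. By its wording, the readmission endpoint counts planned admissions together with returns for complications, and the eligibility rules allow such admissions to occur. If they are equally frequent in both arms, they dilute a real difference in complication-related readmission.

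The amount is unknown. The fall in power from about 60% to between 43% and 26% rests wholly on assumed rates of 6% versus 14% and on 5% to 15% planned admissions that are independent and equal between arms. The document supports neither a biased comparison, nor a faulty window, nor incomplete follow-up.

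One secondary endpoint is affected. The primary endpoint, its analysis and N = 276 are untouched. Severity is minor.

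**What to change.** Add one planned/unplanned field for each rehospitalization, where planned means booked before, or independently of, any complication. Make unplanned readmission within 30 days of discharge the main readmission endpoint and report the all-cause rate beside it as support. The discharge start and the 30-day length can stay.

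Show deaths before discharge as a separate category among all randomised patients, so that the rate is not read as if everyone could be readmitted. Optionally, add days alive and out of hospital to postoperative day 90. It includes deaths, does not depend on when the patient is discharged, and uses dates already needed for readmission and 90-day mortality.

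The cost is one field in the case report form and one reworded secondary endpoint. The downside is that unblinded staff make the classification. A definition fixed in advance limits this, and the retained all-cause rate lets a reader check whether the conclusion depends on it.

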### Randomization

After completion of all the screening evaluations and the CGA, a second visit will be performed. All eligible patients will be randomly assigned to one of the treatment arms after ensuring that all the inclusion criteria are satisfied, none of the exclusion criteria apply, and the patient gave his nonopposition to participate in the study. The randomization will be performed electronically on the Cleanweb site (https://cleanweb.aphp.fr/Ctms-02/portal/login). To obtain homogeneous populations among treatment arms, patients will be randomized by minimization (in a 1:1 ratio) owing to the following stratification factors: (i) investigator center; (ii) colon tumour location (right or left side, with respect to the splenic flexure); (iii) stage IV colon cancer (excluding peritoneal disease); (iv) age (75–85 years vs. >85 years).

### Intraoperative and postoperative management

Neither patients nor health-care providers will be blinded to patient groupings.

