### Statistical analysis and sample size

This study is multicenter, open-label randomized, 2-arm phase III superiority trial, comparing arm A (colectomy by laparoscopy) versus arm B (colectomy by laparotomy) for patients aged 75 years old or more with uncomplicated colon cancer. The hypotheses for sample size calculation are: (i) H0: there is no difference in overall postoperative morbidity between the two arms; (ii) H1: there is a significant difference, with estimated global morbidities in the laparoscopy and laparotomy groups of 20 and 35%, respectively. With a two-sided α risk of 5% and a power of 80% (β = 0.20) as alternative hypothesis H1, 276 patients will be included in total (138 patients in each arm). No interim analysis will be performed. The endpoints will be analyzed according to the intention-to-treat principle, in such a way that patients who did not receive their allocated surgical procedure were analyzed in the treatment group to which they had been randomized. An additional as-treated analysis will also be done, taking into account intraoperative conversions to the open-surgery group.

Continuous variables will be described via the mean, standard deviation, median, minimum and maximum. Categorical variables will be described using frequencies and percentages. The percentages will be calculated with the missing data item. 95% confidence intervals (95% CI) will be calculated when necessary.

Percentage differences between groups will be compared with the Pearson’s χ^2^ test or Fisher’s exact test, as appropriate. Comparison of continuous data will be done by use of the Student’s t test or the nonparametric Mann-Whitney U test, depending on their distribution. Two-tailed *P*-values <0.05 will be considered statistically significant.

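### The only blinding rule exempts no health-care provider, so the pathologist may know the arm when grading the mesocolon, although the specimen can be read without it

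*Protocol article*

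**What the plan says.** The protocol article describes (Protocol overview) a "multicenter, open-label randomized, 2-arm phase III superiority trial comparing laparoscopic or open colectomy". Its one statement about who is masked opens the section Intraoperative and postoperative management: "Neither patients nor health-care providers will be blinded to patient groupings".

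The Endpoints section says of the primary endpoint: "Postoperative morbidity will be collected by an independent observer, using a standardized collection form during hospitalization". That observer is called independent; whether the observer is masked is not said.

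The same section lists the histological criteria for quality of resection: "number of lymph nodes harvested, R0 resection and mesocolic resection quality in 3 grades". It also lists "evolution of geriatric scores (MMS, ADL scale, IADL scale, GDS and TGUG test) at 3 months postoperatively in both arms". For neither does it say who makes the assessment or whether that person knows the arm. The only geriatric assessor named is the one at baseline, in Protocol overview, where the assessment "must be performed within 30 days before the randomization by a geriatrician of the investigator center".

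**The concern.** Surgeons, anaesthetists, ward staff and patients cannot realistically be masked to laparoscopy versus laparotomy. The same does not hold for everyone who produces endpoint data. The blinding sentence speaks of health-care providers as a class, and a pathologist is one in the ordinary sense of the term. The rule is therefore wider than the intervention requires.

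The mesocolic grade is the clearest case. It is an ordinal human judgement made on the specimen, away from the patient and the wound, and the reader needs to know the type of colectomy but not the approach. The node count is less open to judgement, though it depends partly on how thoroughly the specimen is searched.

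What is at stake is the reading of the resection-quality results. If an expectation about one approach shifts the grade in one arm, the comparison shows a difference that is not there or hides one that is, and no analysis can separate this from a real effect afterwards. The 3-month geriatric scores raise a similar but weaker question: baseline is scored before randomization and so without knowledge of the arm, whereas the follow-up score has no stated protection.

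**Working it through.** **1. Passages side by side**

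| Endpoint | Who assesses, as stated | Masking stated | Could the assessor work without the arm? |
|---|---|---|---|
| 30-day morbidity (primary) | Independent observer, standard form | No | Not examined here |
| Mesocolic grade, node count, R0 | Not stated | No | Yes: read on the specimen |
| MMS, ADL, IADL, GDS, TGUG at 3 months | Not stated (geriatrician named at baseline only) | No | In part: the patient is unblinded |

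The only general rule is that health-care providers are not blinded. Nothing in the article takes the pathologist out of it.

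**2. The plan's own figure**

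Statistical analysis and sample size gives "estimated global morbidities in the laparoscopy and laparotomy groups of 20 and 35%, respectively", two-sided α of 5%, power of 80%, and 138 patients per arm (276 in total). With pooled variance and no continuity correction:

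n = [1.960·√(2·p̄(1−p̄)) + 0.842·√(p₁(1−p₁) + p₂(1−p₂))]² / (p₁−p₂)²

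with p₁ = 0.35, p₂ = 0.20, p̄ = 0.275. This gives 137.9, so 138 per arm and 276 in total; power at 138 per arm is 80.0%. The figure reproduces. It concerns morbidity only, so masking the reader of a secondary endpoint does not change it.

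**3. Illustration of sensitivity to differential grading**

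Inputs: n = 138 per arm and two-sided 5% from the article. Assumed, because the article gives no such figures: the true rate of the best grade (70%, range 60 to 80%), the same in both arms; a grading shift in one arm; and analysis of best grade versus the other two. The article specifies three grades and no dichotomy.

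The probability of a significant result in the direction of the shift d is approximately

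Φ[(d − 1.960·s₀)/s₁], with s₀ = √(2·p̄(1−p̄)/n) and s₁ = √((p₁(1−p₁) + p₂(1−p₂))/n);

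the small opposite tail is added.

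- 70% vs 75%: s₀ = 0.0538, s₁ = 0.0537; (0.05 − 0.1053)/0.0537 = −1.03; about 15%.
- 70% vs 80%: s₀ = 0.0521, s₁ = 0.0518; (0.10 − 0.1022)/0.0518 = −0.04; about 48%.

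| True rate | Shift 2 points | 3 points | 5 points | 10 points |
|---|---|---|---|---|
| 60% | – | – | 14% | 41% |
| 70% | 6.5% | about 9% | 15% | 48% |
| 80% | – | – | 19% | 64% |

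With no shift the rate is 5%. The table shows how the test would respond if such a shift existed. It does not estimate a shift in this trial.

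**The case against.** The strongest case against is that the blinding sentence stands at the head of the section on perioperative care, directly before the two surgical arms. Read there, it may mean only those who deliver care. The Endpoints section, where assessment belongs, does not say that the pathologist or the 3-month assessor is told the arm. Who sees the pathology request is also the kind of detail that a condensed article may leave to the full protocol. And the article shows attention to observers: an independent one collects morbidity, and delirium is assessed with a validated instrument.

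Part of this stands. A reader might infer that the specimens will be graded with the arm known. The text does not say so; it leaves that possible. The point is nevertheless more than an omission, because the article states a rule for health-care providers without exception, and that rule is wider than it needs to be.

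A reader might also infer that both assessments could be masked at no cost. The documents do not support this. The request form has to change, masking will sometimes fail, and at centres where one geriatrician follows the patient throughout, a masked 3-month score could need a second assessor.

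The objection carries most weight for the geriatric scores. Patients know their operation and may mention it; the GDS rests on their own answers, and ADL and IADL largely on patient or carer report; TGUG is timed. Masking the rater leaves the patient's own knowledge in place.

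Finally, the shifts in the illustration are assumed, and small ones do little: 2 points raise the false-positive rate only to about 6.5%.

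**Conclusion.** The point holds for the mesocolic grade: the article's only blinding rule excepts no health-care provider, no masked reading is described, and the grade can be given without knowledge of the approach. For the 3-month geriatric scores it holds only as a measure to take where existing staff allow.

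The size of any bias cannot be derived from the documents. Under the stated assumptions (true rate 70%, 138 per arm, best grade against the rest), the false-positive rate would be about 6.5 to 9% for shifts of 2 to 3 points, 15% for 5 points and 48% for 10 points, against a nominal 5%.

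A reader might infer that this endpoint has to prove that laparoscopy does not compromise the resection. The article gives it no confirmatory or non-inferiority role; its hypotheses and sample size concern 30-day morbidity. This is therefore a cheap improvement to a secondary endpoint and no threat to the primary analysis or to the 276 patients planned.

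**What to change.** Limit the blinding sentence in Intraoperative and postoperative management to patients and the surgical, anaesthetic and ward teams. Then add under Endpoints:

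- The pathology request for trial specimens gives the trial number and the type of colectomy, but neither the approach nor the arm. The mesocolic grade and node count are recorded before the operative report is seen.
- Where existing staff allow, the 3-month geriatric scores are taken by an assessor not told the arm, and the patient is asked not to disclose it. The text should say that this reduces rater bias only.

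The cost is a change to the request form and an instruction to the assessors. Masking will fail now and then, through the look of the specimen or a patient's remark. Treatment, visits, sample size and the primary analysis stay as they are.
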